***III.2. Eligibility criteria***

**As stated above, we intend to enroll research subjects at higher-than-average risk of requiring antidiabetic medications in their lifetime.** Keeping in mind the possible side effects of the study drugs (glipizide and metformin), we will adhere to the following inclusion and exclusion criteria:

Inclusion criteria:

- Male or non-pregnant female > 18 years of age
- We will target preferentially people at risk of diabetes or requiring diabetes meds
  - The first tier of risk will be illustrated by one of the following variables (e.g. established type 2 diabetes on diet therapy alone, elevated random glucose in electronic medical record, PCOS, metabolic syndrome, obesity, history of gestational diabetes, etc.)
  - The second tier of risk will be illustrated by other features that correlate with diabetes risk, such as a history of hypertension or dyslipidemia
- Otherwise healthy subjects may also be candidates for the study.
- Able and willing to give consent relevant to genetic investigation

Exclusion criteria:

- Pregnant, nursing or at risk of becoming pregnant
- Currently taking any medications for the treatment of diabetes
- Currently on metformin for any other indication (e.g. PCOS)
- Onset of diabetes before age 25, with autosomal transmission of diabetes across three generations
- History of liver or kidney disease
- Known severe allergic reactions to sulfonamides
- History of porphyria
- Documented estimated glomerular filtration rate (GFR) < 60 ml/min/1.73 m^2^, based on the most recent serum creatinine measurement available in the electronic medical record, and calculated by the Modification of Diet in Renal Disease equation ([81](#_ENREF_81)) available at <http://www.nephron.com/cgi-bin/MDRD_GFR.cgi>
- Currently taking medications known to affect glycemic parameters, such as glucocorticoids, growth hormone or fluoroquinolones
- Planned radiologic or angiographic study requiring contrast within one week of completion of this study
- Established coronary artery disease (CAD), defined as:
  1. History of myocardial infarction.
  2. History of revascularization (coronary artery bypass grafting, percutaneous coronary intervention (e.g. stenting or balloon angioplasty).
  3. Evidence of ischemia on cardiac stress test.
- Enrolled in any other interventional study at time of screening through completion of study protocol
- History of bariatric surgery
- History of seizures
- History of stroke/CVA

1. **Subject Enrollment**

**Eligible patients will be identified by review of electronic data queried from the central data repositories (labs, visits, billing diagnoses) and electronic medical records (problem lists, medications, diagnoses) using previously validated methods.** Some subjects will also be identified from lists of participants from previous research studies. Primary care physicians will be given a single list of their own patients with the option to exclude patients deemed inappropriate for contact. A letter co-signed by the patient’s primary care physician and the study PI will then be sent to each subject explaining the general idea for the study in simple terms, with a stamped postcard and phone number providing an option to either “opt-in” or “opt-out”. In the event that the subject has been recommended by a collaborator, previously participated in a research study at a Partners network site, and gave consent to be contacted in the future; we will substitute their PCP signature with that of the recommending study PI. If the potential research subject has not declined further contact in 2 weeks, the study staff may call him/her and invite him or her to participate in the study. Prior experience with this approach by our group has yielded a 15% initial decline rate and 75% final calculated response rate. Subjects who agree to participation will be further screened via telephone with a brief questionnaire, sent further information and an informed consent form in the mail, and invited to come to the first visit. In addition, flyers will be posted in the internal medicine clinics and the study will be advertised via Partners email. Materials will be prepared both in English and in Spanish; for subjects who request another language arrangements will be made with a translation service.

1. **Study Procedures**

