**We therefore propose the following Specific Aims:**

Specific Aim No.1: To examine the acute response to a sulfonylurea challenge (glipizide 5 mg orally) in subjects at risk of diabetes or with early diabetes (on diet treatment alone), depending on genotype at *KCNJ11* E23K, *TCF7L2* rs7903146, or newly discovered variants linked to type 2 diabetes via associations with related phenotypes, individually or in aggregate

- We hypothesize that subjects with a subset of variants will have an attenuated response, whereas those with a different subset will have no discernible impact on this response

Specific Aim No. 2: To examine the acute response to short-term metformin treatment on the insulin sensitivity index in the same group, depending on genotype at *KCNJ11* E23K, or newly discovered variants linked to type 2 diabetes via associations with related phenotypes, individually or in aggregate

- We hypothesize that subjects with a subset of variants will have a diminished improvement in insulin sensitivity compared to non-carriers

Specific Aim No. 3: To examine acute insulin secretion (by the insulinogenic index derived from an OGTT), GLP-1 and glucacon levels, and metabolomic profiling after short-term metformin treatment (500 mg bid x 4 doses) in the same group of subjects, depending on genotype at *TCF7L2* rs7903146, or newly discovered variants linked to type 2 diabetes via associations with related phenotypes, individually or in aggregate

- We hypothesize that subjects with the risk TT genotype at *TCF7L2* rs7903146, or a subset of variants will have a reduced insulinogenic index and GLP-1 levels than non-carriers

***If successful, this proposal should help clarify the pathophysiologic mechanisms by which these key genetic variants increase risk of type 2 diabetes, and assess their impact on commonly used antidiabetic treatments. In addition, this pilot study will lay the groundwork for a long-term, outcomes-based pharmacogenetic clinical trial.***

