# Subject Selection

***III.1. Available samples***

**Our goal is to recruit research subjects likely to require antidiabetic medications in their lifetime.** These include individuals with early type 2 diabetes (on diet treatment alone), or at higher-than-average risk of developing diabetes (impaired fasting glucose, IGT, a history of gestational diabetes, or suffering from the metabolic syndrome, obesity and/or the polycystic ovary syndrome [PCOS]). We have assembled a local team of collaborators with a shared interest in diabetes and metabolic traits, who have ready access to suitable research subjects.

**Our main target for recruitment will be the local Partners Network practices.** Making use of the electronic medical record available to all 12 MGH-based primary care practices, [name] has compiled a Practice-Based Research Network (PBRN), based on the approximately 90,000 primary care patients with regular care at MGH (i.e. an identified MGH primary care physician *and* a clinic visit in the prior 2 years). This database includes a cohort of 7,692 patients with type 2 diabetes seen between 07/01/04 and 06/30/05. Of those, there were 1,547 patients (20.1%) not on glycemic medication therapy (i.e. diet/lifestyle); their characteristics are shown in Table 1.

| Table 1: Demographic characteristics of diet-treated MGH patients with diabetes | |
| --- | --- |
| Female | 775 (50.1%) |
| Age (years) | 65.3 ± 14.7 |
| Caucasian | 1,202 (77.7%) |
| Current smoker | 230 (14.9%) |
| Coronary artery disease | 382 (24.7%) |
| BMI (kg/m^2^) | 31 ± 7.6 |
| N medications | 7.9 ± 5.2 |
| Clinic visits previous year | 7.6 ± 6.2 |
| HbA_1C_ (%) | 6.7 ± 1.1 |
| Mean blood pressure (mm Hg) | 130/74 |
| LDL cholesterol (mg/dl) | 93.7 ± 32.5 |
| Variables are expressed as n (%) or mean ± SD. | |

**A second possible source of volunteers will be non-diabetic subjects with at least one elevated random glucose (>200 mg/dl).** In addition to the above diet-treated patients with diabetes, [name] has identified another ~1,500 MGH primary care patients who do not carry the diagnosis of diabetes, but have at least one random glucose >200 mg/dl in the medical record. Because hyperglycemia is predictive of future diabetes ([78](#_ENREF_78); [79](#_ENREF_79)), this group is at higher-than-average risk of ever requiring antidiabetic drugs.

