**Other Partners and Joslin collaborators work with susceptible patient populations.** [name] at the MGH Reproductive Endocrine Unit is currently carrying out a study with about 500 patients with PCOS, only a small fraction of whom (~10%) are on current metformin treatment. Drs. [name] and [name] have an established research program on the metabolic syndrome which comprises approximately 100 subjects with and without HIV infection. [name] has been following a cohort of ~200 women with a history of gestational diabetes mellitus (GDM) ([80](#_ENREF_80)). Finally, we have access to 1,004 non-diabetic subjects formerly enrolled in a Partners-Roche Consortium who have consented to diabetes-related genetic investigation, 25% of whom have BMI >30 kg/m^2^. These cohorts can be further expanded, if necessary, with additional help from the MGH and Brigham Obesity Clinics. At the Joslin Diabetes Center, family members of the diabetic patients will also be recruited.

As the study aims to test the effect of specific genetic variants on pharmacological response, recruitment efforts will also include queries within an institutional biorepository containing samples adequate for genotyping and demographic information on individuals interested in participating in clinical trials. Individuals who have already indicated interest in participating in future studies and given consent for genotype-directed call back into future research studies will be contacted first by mail to assess their interest in participating in SUGARMGH and then, unless otherwise indicated, by phone.

In the event that an individual does not qualify to participate in the study, we will ask if they would like to be contacted by collaborators involved in other research studies.

In the event that recruitment lags, we will advertise outside of the Partners and Joslin networks. This may include posting flyers, internet advertising, newspaper ads and any other forms of displaying the approved flyer.

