***VI.1. Study endpoints***

**The study will have the following primary endpoints, according to each Specific Aim:**

Specific Aim No. 1 – Sulfonylurea challenge: Trough glucose and peak insulin levels will be compared by genotype. Secondary endpoints will be differences in glucose and insulin areas under the curve (AUC, calculated by the trapezoidal method), as well as glucose and insulin at 2 hours. Leftover serum samples will be frozen for glucagon level measurements.

Specific Aim No. 2 – Acute metformin effect on insulin sensitivity: The insulin sensitivity index (reciprocal of insulin resistance by homeostasis model assessment ([84](#_ENREF_84))) will be calculated as 22.5/[fasting insulin x (fasting glucose/18.01)], and compared by genotype. A secondary endpoint will be differences in the insulinogenic index by genotype after metformin treatment, calculated as [(insulin at 30 min) – (insulin at 0 min)]/[(glucose at 30 min) – (glucose at 0 min)].

Specific Aim No. 3 – insulinogenic index and GLP-1 levels during OGTT: The insulinogenic index, calculated as above, will be compared by genotype, and the differences between genotypic groups will be contrasted to those observed during the sulfonylurea challenge (Specific Aim No. 1). A subset of subjects (selected to have equal numbers in each genotypic group) will have their GLP-1 levels measured, and peak GLP-1 as well as AUC will be compared by genotype. Leftover serum samples will be frozen for metabolomic profiling and glucagon level measurements.

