***VI.2. Statistical analysis***

**Non-normal variables will be log transformed.** They will be adjusted for age, gender and BMI, and residuals will be compared between each group of homozygous individuals at each locus by Student t tests. Since these polymorphisms may influence glycemic traits by affecting BMI, both BMI-adjusted and unadjusted analyses will be reported. Secondary analyses will include exploration of genetic models (dominant, recessive or additive), by including heterozygous individuals and performing ANOVA across the three genotypic groups, with subsequent Bonferroni adjustment for multiple comparisons. The role of self-reported ethnicity will be evaluated with an interaction term; analyses will also be repeated within each self-reported ethnic group, and in the aggregate of groups where minor allele frequencies are comparable. As these experiments involve validation of previous hypotheses, nominal *P* values below 0.05 will be considered statistically significant.

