***VII.1. Risks to the subjects and implementation of safeguards***

**We will enroll 1,000 male or non-pregnant female adults with early type 2 diabetes (on diet treatment only).** No vulnerable populations will be enrolled. Although glipizide is labeled as a pregnancy Class C drug and metformin as a Class B drug, no pregnant or nursing women will be enrolled; in part, this is due to the known alterations in glycemic physiology during pregnancy. Women at risk of being pregnant (i.e. sexually active without adequate birth control) will receive a urine pregnancy test before enrollment.

**In order to avoid an exaggerated response to either of the two study medications, we will exclude subjects with impaired renal or hepatic function.** This will be initially determined by both history and examination of the medical record, which will be available to us due to our exclusive use of the Partners-specific source database. Renal dysfunction will be defined as a decrease in estimated GFR < 60 ml/min/1.73 m^2^, based on the most recent serum creatinine measurement available in the electronic medical record (within the past year), and calculated by the Modification of Diet in Renal Disease equation ([81](#_ENREF_81)). Subjects with advanced diabetes (i.e. on antidiabetic medications), type 1 diabetes (i.e. on insulin therapy) or suspected Maturity Onset Diabetes of the Young (based on age at diagnosis and familial transmission) will also be excluded. Finally, subjects with a history of porphyria or severe sulfonamide allergy will be excluded to avoid potential hypersensitivity reactions to glipizide.

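### The protocol describes its population in incompatible ways, and for Aims 1 and 2 the genotype comparison of absolute post-drug values can pick up case mix and starting glycemia as well as drug response

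*Protocol*

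**What the plan says.** **Population.** Specific Aim 1 places the study "in subjects at risk of diabetes or with early diabetes (on diet treatment alone"), and Aims 2 and 3 use the same group. Section III.1 agrees: "These include individuals with early type 2 diabetes (on diet treatment alone), or at higher-than-average risk of developing diabetes". Section III.2 goes wider. It adds a second tier (hypertension, dyslipidemia) and then says "Otherwise healthy subjects may also be candidates for the study", with no quota for any group. Section VII.1 says something else: "We will enroll 1,000 male or non-pregnant female adults with early type 2 diabetes (on diet treatment only").

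**Endpoints.** For Aim 1, section VI.1 states: "Trough glucose and peak insulin levels will be compared by genotype". For Aim 2, the insulin sensitivity index "will be calculated as 22.5/[fasting insulin x (fasting glucose/18.01)], and compared by genotype". Neither is defined as a change from Day 1 or adjusted for it, although section V.2 draws fasting glucose and insulin on Day 1 before any study drug.

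**Analysis.** On covariates, section VI.2 states: "They will be adjusted for age, gender and BMI". Residuals are then compared between the two homozygote groups by t test. BMI may lie on the path from genotype to trait, so results are to be given with and without it. Self-reported ethnicity is the only other factor examined. Diabetes status does not appear.

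**The concern.** The two population statements lead to different trials. If everyone has diet-treated diabetes, the share with diabetes cannot differ by genotype. If at-risk and healthy people also enter, it can, because both named loci were selected for their association with diabetes (sections I.1 and I.3).

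In the mixed sample, risk homozygotes will tend to include more people with diabetes. Those people start from higher glucose, and the Aim 1 and Aim 2 endpoints are absolute levels, so the starting difference passes into what is called response. For E23K the shift raises trough glucose in KK, which looks like the attenuated glipizide response that Aim 1 anticipates. For TCF7L2 it can create a trough-glucose difference at a locus where section II expects the sulfonylurea effect on insulin secretion not to depend on genotype.

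**Working it through.** **The plan's own figures.** Section VI.3 gives risk-allele frequencies of 0.32 (TCF7L2) and 0.35 (E23K) and risk-homozygote shares of about 10% and 12%. Hardy-Weinberg gives 0.32² = 0.1024 and 0.35² = 0.1225, so the shares reproduce. At N = 750 the groups are TT 77 and CC 347, KK 92 and EE 317.

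**Inputs from the protocol.**
- E23K: allelic odds ratio 1.15 (I.1), so 1.15² = 1.3225 between homozygotes.
- TCF7L2, higher: allelic relative risk 1.56 (I.1), reported for the linked microsatellite and used here as an odds ratio, so 1.56² = 2.43 between homozygotes.
- TCF7L2, lower: hazard ratio 1.55 between rs7903146 homozygotes (I.3.b), used as an approximate odds ratio, with heterozygotes at √1.55 = 1.245.

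**Assumptions, not in the protocol.** The diabetic share D of the sample is 10%, 25% or 50%. Trough glucose is 20-40 mg/dl higher in people with diabetes. Non-diabetic genotypes follow Hardy-Weinberg at the stated frequencies.

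**Formula.** For genotype g with Hardy-Weinberg frequency h and relative odds w, the frequency among people with diabetes is c = h·w / Σ(h·w). The diabetic share within the genotype is D·c / [D·c + (1−D)·h]. The false difference is the share gap between homozygotes times the trough gap.

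The sums Σ(h·w) are:
- TCF7L2, lower: 0.4624 + 0.4352×1.245 + 0.1024×1.55 = 1.163
- TCF7L2, higher: 0.4624 + 0.4352×1.56 + 0.1024×2.43 = 1.390
- E23K: 0.4225 + 0.4550×1.15 + 0.1225×1.3225 = 1.108

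**Example (TCF7L2, lower, D = 25%).** In TT, c = 0.1024×1.55/1.163 = 0.1365, and the share is 0.25×0.1365 / (0.25×0.1365 + 0.75×0.1024) = 30.8%. In CC, c = 0.4624/1.163 = 0.3976, and the share is 22.3%. The gap is 8.5 points, and 0.085 × 30 = 2.5 mg/dl.

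| Locus and effect | Share gap at D = 10 / 25 / 50% (points) | False difference at a 30 mg/dl gap (mg/dl) | Range over 20-40 mg/dl |
|---|---|---|---|
| TCF7L2, 1.55 between homozygotes | 4.2 / 8.5 / 10.9 | 1.3 / 2.5 / 3.3 | 0.8-4.4 |
| TCF7L2, 1.56 squared | 8.9 / 17.5 / 21.8 | 2.7 / 5.3 / 6.5 | 1.8-8.7 |
| E23K, 1.15 squared | 2.6 / 5.3 / 7.0 | 0.8 / 1.6 / 2.1 | 0.5-2.8 |

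**Scale.** Section VI.3 powers the challenge for a 10% difference in trough glucose, which is 7-9 mg/dl at an assumed trough of 70-90. Its claim of more than 99% power (one-sided 0.05) for TT against CC needs a coefficient of variation of at most 0.10 / [(1.645 + 2.326) × √(1/77 + 1/347)] = 20%. At an assumed trough of 80 mg/dl that is an SD of 16 and a standard error of 16 × 0.126 = 2.0 mg/dl. A shift of 2.5 mg/dl is then 1.25 standard errors. With no genotype effect on response, a two-sided 5% test would reject about 24% of the time. For E23K the standard error is 16 × 0.1185 = 1.9, and a shift of 1.6 mg/dl gives about 13%.

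**The case against.** **Much of the assumed trough gap is a fasting gap.** It existed before glipizide, so the absolute endpoint is at fault as much as the missing status term. This stands. Adjusting for the Day 1 value would absorb much of it, and adjusting for status alone would be an incomplete remedy.

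**The TCF7L2 input of 1.56 is at the high end.** This stands: the protocol's own homozygote figure for rs7903146 halves the result. The non-diabetic recruits are largely high-risk people, probably carrying more risk alleles, which narrows the contrast further. Table 1 shows mild disease (mean HbA1c 6.7%), so a trough gap below 20 mg/dl is plausible. At 10 mg/dl the lower TCF7L2 shift is 0.042 × 10 to 0.109 × 10, about 0.4-1.1 mg/dl. BMI adjustment may also remove part.

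**Diabetes status lies downstream of genotype.** This stands too. Conditioning on it can remove a mediated effect and introduce some selection bias. It is also imperfectly known, because section III.1 recruits undiagnosed people with a random glucose above 200 mg/dl and section VII.1 expects to uncover undiagnosed diabetes. Status therefore should not replace the planned analysis.

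**Such analyses are often left to a statistical analysis plan.** This does not dispose of the point, because section VI.1 fixes the endpoints and section VI.2 fixes the covariates and the test.

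**A reader might extend the point to Aim 3.** The protocol does not support that. Aim 3 hypothesises a lower insulinogenic index and lower GLP-1 in TT, so a genotype difference there is the expected finding and not a false drug response.

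**Conclusion.** The contradiction between section VII.1 and the Aims and section III is definite and needs correcting whatever the analysis. The case-mix point holds for Aims 1 and 2: as written, a homozygote difference in trough glucose, peak insulin or the index on metformin cannot be attributed to drug response alone.

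The size is uncertain, because the diabetic share and the trough gap are assumed. For TCF7L2 it runs from under 1 mg/dl to nearly 9, and the protocol's own homozygote estimate puts it at 0.8-4.4. For E23K, the locus of the main glipizide hypothesis, it is modest at 0.5-2.8 mg/dl against a design difference of about 7-9. All of these shrink if the trough gap is smaller.

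A reader might infer that any variant without an effect on response must still show a difference in every endpoint. The documents do not support that. Only trough glucose can be sized here, and no corresponding figure was derived for peak insulin or the index.

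**What to change.** 1. State one population, in the same terms, in the Specific Aims and in sections III.1, III.2 and VII.1.
2. In section VI.2, for Aims 1 and 2, keep the planned comparison. Beside it, report the genotype comparison adjusted for the Day 1 value (glucose, insulin or the index, as the endpoint requires) and for diabetes status at enrolment (yes/no). Show results by status as well. This follows the plan's existing practice of reporting with and without BMI.
3. State that a genotype difference will be read as drug response only if it persists in the adjusted analysis.

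The cost is a few sentences and slightly fewer degrees of freedom. Day 1 glucose and insulin are already drawn, and status comes from the medical record and the history taken at Visit 1. Results by status lose some precision. If 70% of 750 were non-diabetic (assumed; KK 64, EE 222) and the coefficient of variation were 20%, one-sided power for a 10% trough difference would be about 97%, against about 99.5% in the full sample. Because the adjusted result may remove a mediated effect or carry some selection bias, both versions should be reported.
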